## Abstract

**Background:**

Cognitive impairment frequently co-occurs with type 2 diabetes but is often undiagnosed. Cognitive impairment affects self-management leading to treatment-related complications.

**Objective:**

The aim of this study is to develop a stepped diagnostic procedure, consisting of a screening test complemented by an evaluation by a general practitioner (GP), to detect undiagnosed cognitive impairment in older people with type 2 diabetes.

**Methods:**

The accuracy of two self-administered cognitive tests, the “Test Your Memory” (TYM) and “Self-Administered Gerocognitive Examination” (SAGE) alone, and in combination with an evaluation by a GP will be assessed. A diagnosis of mild cognitive impairment (MCI) or dementia at a memory clinic will serve as reference standard. This cognitive impairment in diabetes (Cog-ID) study will include 513 people from primary care facilities aged ≥70 with type 2 diabetes. The participants will first fill out the TYM and SAGE tests, followed by a standardized GP evaluation for cognitive impairment, including a mini mental state examination (MMSE). Subsequently, participants suspected of cognitive impairment (on either test or the GP assessment) and a random sample of 15% (65/435) of participants without suspected cognitive impairment will be referred to the memory clinic. At the memory clinic, a medical examination, neuropsychological examination, and magnetic resonance imaging (MRI) of the brain will be performed. Participants will also fill out questionnaires assessing health status and depressive symptoms at baseline and after 6 and 24 months.

**Results:**

This research obtained funding and ethical approval. Enrolment started in August, 2012, and all study-related activities will be completed in September, 2016.

**Conclusions:**

With the results from this study, physicians will be able to detect cognitive impairment affecting type 2 diabetes patients through case-finding, and can use tailored care to reduce associated complications. Additionally, the results may stimulate discussions about cognitive impairment and whether early recognition is desirable.

## Introduction

### Background

Patients with type 2 diabetes have an increased risk of cognitive impairment and a doubled risk of dementia compared to people without diabetes [1,2]. Cognitive impairment often remains unrecognized by physicians, even when patients or their relatives express complaints [3,4]. This is an important problem since in patients with type 2 diabetes, cognitive impairment is associated with impaired self-management and an increased incidence of diabetes-related complications [5,6]. Early recognition of cognitive impairment could assist the general practitioner (GP) in taking appropriate, personalized measures in diabetes management to prevent complications [7].

Routine screening for cognitive impairment in elderly patients with type 2 diabetes has been advocated [8]. The American Diabetes Association advises to individualize diabetes treatment and to adjust management to the preserved capacity of patients, thereby specifically taking into account cognitive functioning [9]. However, compared with other potential complications and co-morbid conditions of type 2 diabetes, the diagnostic evaluation of diabetes-associated cognitive impairment is underdeveloped. While screening algorithms have been established for microvascular complications, such as retinopathy or nephropathy, there is no established method to detect undiagnosed cognitive impairment. The ideal procedure for the assessment of possible disturbances of cognitive functioning should be easy and quick to perform. The procedure should readily identify people who require further, more elaborate and time consuming, evaluations by the GP or possibly referral to a memory clinic. Unfortunately, administration of most cognitive tests already requires a lot of time from a physician, nurse, or other health care worker. In addition, currently available tests with the shortest administration times tend to cover only certain aspects of cognition, particularly those affected in Alzheimer’s disease. Moreover, these tests are much less accurate in identifying people with other conditions, in particular vascular cognitive impairment [10].

These issues may be resolved by the recent introduction of self-administered cognitive tests, such as the Test Your Memory (TYM) [11] and the Self-Administered Gerocognitive Examination (SAGE) [12] tests. In a memory clinic setting, these tests have been shown to measure a broader range of cognitive domains than the mini mental state examination (MMSE) and they were also able to detect mild cognitive impairment (MCI) [11-13]. Therefore, in our view, these self-administered cognitive tests could be promising tools for the detection of cognitive impairment in type 2 diabetes in primary care.

The ultimate goal of a diagnostic procedure for cognitive impairment is to improve clinical outcomes and patients' quality of life. However, before the effect of a diagnostic procedure can be evaluated, which specific tests to include must be determined. The latter is examined in this cognitive impairment in diabetes (Cog-ID) study. Here, we aim to establish a reliable, valid, and efficient stepped diagnostic procedure to detect cognitive impairment in patients ≥70 years of age with type 2 diabetes, starting with the TYM and the SAGE tests. It is unknown which of these two tests is best suited for application in a primary care setting; therefore we will assess the accuracy and feasibility of both. In addition, we will describe how early detection of cognitive impairment affects treatment and quality of life in an observational study that is part of the main study. Together, the results will help shape future studies with the goal of answering the unresolved, but increasingly relevant and heavily debated question [14], whether early recognition of cognitive impairment in patients with type 2 diabetes will help the GP to take appropriate measures in disease management, and ultimately prevent treatment-related complications. Future studies are needed to assess the effect of the established diagnostic procedure on clinical outcomes in a randomized controlled trial.

### Objectives

Our overall aim is to establish a reliable, valid, and efficient stepped diagnostic procedure to detect undiagnosed cognitive impairment in patients ≥70 years of age with type 2 diabetes. The procedure will consist of a self-administered cognitive test and an evaluation by a GP. Additionally, we will describe how early detection of cognitive impairment affects treatment and quality of life in participating patients in a parallel observational study. The specific objectives of the study are (1) to assess the validity of two self-administered cognitive tests (TYM and SAGE) in detecting undiagnosed cognitive impairment in elderly patients with type 2 diabetes in a primary care setting and to select the best instrument, (2) to assess the diagnostic accuracy of a standardized evaluation by a GP in detecting undiagnosed cognitive impairment in patients with type 2 diabetes, (3) to estimate the accuracy and efficiency of the best cognitive test(s) combined with the evaluation by the GP, and (4) to describe the effect of the diagnostic procedure on several aspects of diabetes care (ie, treatment targets and appointment schedules) and patients’ quality of life.

## Methods

### Study Participants

General practitioners (GPs) in the surroundings of Utrecht, the Netherlands, will be asked to select patients with type 2 diabetes mellitus ≥70 years of age. Exclusion criteria include a diagnosis of dementia, previous investigation at a memory clinic, and the inability to write or read in Dutch. Patients with a disorder that might influence cognitive functioning, like substance abuse or a psychiatric or neurological disorder, but without a diagnosis of cognitive impairment are not excluded as we are interested in the presence of unknown cognitive impairment regardless of the cause. Eligible patients will receive a letter from their GP with information regarding the study. Patients will be asked to return the response form on which they can mark whether or not they are willing to participate. In the case of non-response, one reminder will be sent.

### Screening Tests

#### Test Your Memory Test

The TYM is developed to test a range of cognitive functions and consists of 10 tasks [11]. It is a self-administered test and takes a patient around 5 minutes to complete. The tasks include orientation (10 points), ability to copy a sentence (2 points), semantic knowledge (3 points), calculation (4 points), verbal fluency (4 points), similarities (4 points), naming (5 points), visuospatial abilities (2 tasks, total 7 points), and recall of a copied sentence (6 points). The ability to complete the test without help is an 11^th^ task (5 points); because of our study design all patients will receive these 5 points. The maximum score is 50 points. A score of ≤39 is suggestive of dementia [11]. The TYM was translated into Dutch and then translated back to English by a bilingual native English speaker, which resulted in a version almost identical to the original.

#### Self-Administered Gerocognitive Examination

The SAGE measures cognitive functioning in the domains of orientation (4 points), language (4 points), memory (2 points), executive function (4 points), calculations (2 points), abstraction (2 points), and visuospatial abilities (4 points) [12]. Furthermore, the SAGE includes several questions on demographic information, medical and family history, and current status. The maximum score is 22 points. A score of ≤14 is suggestive of dementia [12]. Like the TYM, the SAGE was translated into Dutch and then back into English, which resulted in a version almost identical to the original.

### The Diagnostic Strategy

#### Part 1: Home Visit

Participants will be visited at home by a research physician (a trainee GP). The home visit will take about 1 hour. The participant will be asked to fill out the TYM, SAGE, and a questionnaire assessing health status and depressive symptoms, including the Short Form Health Survey (SF-36)[15], EuroQol (EQ)-5D and EQ-VAS [16], and the Center for Epidemiologic Studies Depression Scale (CES-D) [17]. The research physician will be blinded for the scores on the TYM and the SAGE, and will not provide any assistance in filling out the questionnaires. Following the questionnaires, the research physician will administer a standardized diagnostic interview based on the Dutch guideline for case finding of dementia by GPs to both the participant and (if possible) a close informant [18], representing the evaluation by the GP. The interview will include demographic variables, educational level, and living conditions, as well as a medical history and a list of cognitive complaints (Table 1). After the interview, the MMSE will be administered. The MMSE consists of 11 tasks including the domains orientation in time (5 points), orientation in space (5 points), registration of three words (3 points), concentration and calculation (5 points), recall of three words (3 points), language (8 points) and visuospatial abilities (1 point). The maximum score is 30 points with a higher score indicating a higher level of cognitive functioning. A score of ≤24 is suggestive of dementia.

Based on the history taken, the research physician will decide whether the participant should be classified as "suspected of cognitive impairment" or "no cognitive impairment" according to the criteria for MCI and dementia [19,20]. If the MMSE score is ≤24, the participant will always be classified as "suspected of cognitive impairment".

**Table 1 table1:** List of questions about acquired cognitive symptoms for the participant and informant.

Questions		Patient^a^	Informant^a^
Do you have memory problems?			
Do other people think you are forgetful?			
Do you forget names of relatives or peers?			
Do you often lose things?			
Do you have to write more things down to remember it than you were used to?			
Are there activities you stopped doing in the past five years (and why)?			
Do you visit friends or family less often?			
How does cooking, grocery shopping and the household go?			
Do you have trouble managing your finances?			
Do you have trouble driving a car or using public transport?			
Do you need help getting dressed?			
Do you sometimes forget what month or year it is?			
Can you independently manage your medication?			
Can you follow the news in the paper or on television?			
Do you have problems with walking or holding your balance?			
Did you lose weight unintentionally in the past years?			
Has your smell or taste changed in the past years?			
Are you depressive?			
Can you still have pleasure in things?			
Do you have problems with hearing or vision?			

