### Statistical Analysis

The diagnosis of cognitive impairment (MCI or dementia) at the memory clinic will be used as the reference standard. To address the first two objectives, participants will be classified as true positive, false positive, false negative, or true negative separately for the evaluation by the GP, TYM, and SAGE.

Not all of the patients in our study will receive the reference standard, which could lead to partial verification bias [25]. However, if only patients with the reference standard were included in the analysis (complete case analyses), the results would be biased because the selection of the patients with the reference standard will not be at random [25]. A reliable method to reduce this bias is to impute the reference standard [25]. A cognitive impairment diagnosis (yes or no) in the memory clinic will, therefore, be imputed for patients who did not attend the memory clinic. Imputed databases (N=10) will be generated with the predictors TYM, SAGE, MMSE, GP evaluation, as well as age, gender, educational level, living situation, and score on the domain mobility of the EQ-5D. The latter two are chosen because they can influence why some patients did not attend the memory clinic. With these imputed numbers, the sensitivity, specificity, positive predictive value (PPV), and negative predictive value (NPV) will be calculated.

The extent to which the cognitive tests and the evaluation by the GP discriminate between participants with and without cognitive impairment will be determined by the area under the receiver operating characteristic (ROC) curve. Next, the optimal cutoff values of the tests for this population will be determined according to the best combination of corresponding sensitivity and specificity assessed with the Youden index. The Youden index measures the effectiveness of a diagnostic marker and enables the selection of an optimal cutoff point [26]. By means of the ROC curve and the best combination of diagnostic values, the optimal instrument will be selected.

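### If TYM and SAGE are given in the order listed, any practice or fatigue effect falls on SAGE alone, and the article describes no alternation or recording of order

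*Protocol article*

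**What the plan says.** The Abstract (Methods) says "The participants will first fill out the TYM and SAGE tests, followed by a standardized GP evaluation for cognitive impairment". Part 1: Home Visit says "The participant will be asked to fill out the TYM, SAGE, and a questionnaire assessing health status and depressive symptoms", and then places the interview after the questionnaires and the MMSE after the interview. On duration it says "The home visit will take about 1 hour".

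The sections on the two tests show shared domains: orientation, calculation, similarities or abstraction, visuospatial ability and memory.

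Objective 1 is to validate both tests "in a primary care setting and to select the best instrument". Under Statistical Analysis, "the optimal cutoff values of the tests for this population will be determined according to the best combination of corresponding sensitivity and specificity", using the Youden index, and then "By means of the ROC curve and the best combination of diagnostic values, the optimal instrument will be selected". Referral to the memory clinic uses the preset cutoffs of 39 or below on TYM and 14 or below on SAGE (Part 2: Selection Criteria). In the intended stepped procedure, one cognitive test is taken and the GP sees only those who are positive on it.

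The article describes several controls against bias: blinding of the research physician and the clinic staff, an independent selector, withholding clinic results from the research physician to limit a learning effect, and imputation of the reference standard. It describes none for the order of the two tests.

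**The concern.** Objective 1 is a within-person comparison of two tests taken at the same visit by people aged 70 or over. If one test always comes second, its scores include whatever practice or fatigue the first test produced, and the data cannot separate that effect from the difference between the tests.

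Three results could be touched: accuracy and referral at the preset cutoffs; the new cutoff, which would be applied to a test taken alone; and the choice between TYM and SAGE. These are not equally exposed, and the working treats them separately.

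**Working it through.** **1. What fixes the order.** Home Visit lists TYM, then SAGE, then the questionnaires. The Abstract puts both tests before the GP evaluation but does not rank them. TYM-then-SAGE is the natural reading, but it is not stated as a rule.

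**2. The plan's own figures (Sample Size Calculation).** Test positives needed: n = 1.65² × 0.64 × 0.36 / 0.11² = 51.84, rounded up to 52, as stated. Total: 52 × 0.64 / (0.08 × 0.79) = 526.6, within 3% of the stated 513. This point disputes neither figure.

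**3. Effect equal in everyone.** Inputs from the same section: SAGE sensitivity 79%, specificity 95%, prevalence 8%, N = 513. Assumed: normal scores with equal SD in both groups, and a shift of s SD on the second test (positive s means lower scores).

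- Specificity = Φ(1.645 − s)
- Sensitivity = Φ(0.806 + s)
- PPV = 0.08 × sens / [0.08 × sens + 0.92 × (1 − spec)]
- Test positives = 513 × the denominator of the PPV

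| Shift on second test | Sens | Spec | PPV | Positives of 513 |
|---|---|---|---|---|
| none | 79% | 95% | 58% | 56 |
| 0.1 SD worse | 82% | 94% | 54% | 62 |
| 0.2 SD worse | 84% | 93% | 50% | 70 |
| 0.3 SD worse | 87% | 91% | 46% | 78 |
| 0.1 SD better | 76% | 96% | 62% | 50 |
| 0.2 SD better | 73% | 97% | 66% | 45 |
| 0.3 SD better | 69% | 97% | 70% | 41 |

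Two yardsticks from the plan: the lower PPV margin is 53%, which the 0.2 SD worsening passes; and the sensitivities quoted from previous research are 81% (TYM) and 79% (SAGE), a gap of 2 points, against about 3 points for a 0.1 SD shift.

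**4. What an equal effect leaves alone.** The distance between the groups is 1.645 + 0.806 = 2.451 SD for every s. The AUC therefore stays at Φ(2.451/√2) = 0.958, and the maximum Youden index is also unchanged. The Youden cutoff itself moves by s.

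**5. Effect that differs by impairment.** If only impaired participants worsen on the second test, its AUC rises from 0.958 to Φ((2.451 + 0.2)/√2) = 0.970 for 0.2 SD, or 0.978 for 0.4 SD. A simulation of two equally accurate tests shows what this does to the choice. It assumed 41 of 513 impaired, within-group correlation 0.5, everyone verified, selection by higher AUC and 1,500 runs.

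| Effect on second test | Second test chosen, fixed order | Second test chosen, alternated |
|---|---|---|
| none | 51% | 52% |
| impaired worse by 0.2 SD | 77% | 51% |
| impaired worse by 0.4 SD | 93% | 50% |
| unimpaired better by 0.2 SD | 78% | 51% |

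Uniform shifts of 0.2 SD either way gave 47% and 48% under fixed order. Adding a constant to one test cannot change a rank, so the true value is one half and the gap is simulation error.

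**6. Precision of a first-taken comparison.** 513 × 0.08 = 41 impaired, so about 20 per test. The 95% half-width for a sensitivity of 79% is 1.96 × √(0.79 × 0.21 / 20) = 0.18, or 18 points, even with full verification.

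**The case against.** The strongest reply is that the document does not fix an order. Its lists need not follow time: Selection Criteria and Statistical Analysis both name the physician's evaluation before TYM and SAGE, although it takes place after them. Booklet order is also detail that a condensed article may leave to the full protocol. This stands. A reader might infer that SAGE is always taken second; the text makes that likely but does not say it, so the point is conditional.

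Second, a reader might infer that any order effect biases the selection of the best test. It does not: an equal shift leaves the AUC and maximum Youden index unchanged, and selection uses the ROC curve and the best diagnostic values. This also stands. Bias in the choice needs an effect that differs by impairment. That is plausible, but nothing in the documents shows it.

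Third, TYM takes about 5 minutes, so fatigue from it may be slight, and shared domains are not shared items, so practice may be slight too. This is fair and argues for modest shifts, but it does not make them zero.

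Fourth, alternation does not reproduce single-test use, because half of the scores would still come from a second-taken test, and a first-taken comparison is imprecise. Both are correct. Alternation does stop the effect falling on one test only, and recording the order allows it to be estimated.

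**Conclusion.** The concern holds in conditional form. If the tests are given as listed, any order effect falls on SAGE alone and cannot be separated from the difference between the tests. An equal effect would alter referral and accuracy at the preset cutoff and misplace the Youden cutoff for single-test use. Under the assumed 0.1 to 0.3 SD worsening, PPV goes from about 58% to 54%–46%; under a gain of the same size it goes to 62%–70%. An effect that differs by impairment would also tilt the choice of instrument: in the simulation, the second of two equal tests was chosen in 77% of runs at 0.2 SD and 93% at 0.4 SD.

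These figures rest on assumed shifts, a normal model and full verification; the documents supply no size or direction. They show what the design leaves open, not that bias has occurred. The safeguard is worth adopting because it is cheap and protects the comparison in objective 1.

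**What to change.** State the order in which TYM and SAGE are given. Alternate or randomise it by participant number, and record it for each participant. Compare the tests with order taken into account. Report results from the first-taken test as a descriptive check only, given about 20 impaired participants per test. If visits have already begun in one order, alternate from now on and record which participants preceded the change.

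The cost is two versions of the booklet and one extra variable. No further visits or staff are needed, and the sample size stays at 513.

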**The following 3 questions to be completed by the informant**			
	Do you think his/her personality has changed?		
	Did you take over tasks from the participant (and why)?		
	Does he/she repeat things often?		
**Observational points**		**Yes**	**No**
	Inability to find the correct words		
	Many repetitions or hesitations		
	Often does not understand the question		
	Head turning sign		
	Inconsistencies or confabulation		
	Poor grooming		

^a^input fields to be filled in with the answers

#### Part 2: Selection Criteria for Memory Clinic Visit

After the home visit, an independent physician, not involved in the home visit or in the memory clinic, will determine whether the participant will be selected for a visit to the memory clinic of the University Medical Centre Utrecht. To minimize the influence of the increasing experience of the research physician because of the growing number of home visits during the study period, the research physician who visited the participant at home will not be informed about the results of the memory clinic. The following 3 criteria will be used to decide whether a participant will be invited to the memory clinic (1) a classification of “suspected of cognitive impairment” by the research physician, (2) a score of ≤39 on the TYM, and (3) a score of ≤14 on the SAGE. When a participant scores positive on one of these criteria, the participant will be invited to the memory clinic. In addition, a random sample of 15% (65/435) of participants with negative scores on all 3 criteria will be invited to the memory clinic (see sample calculation below and Figure 1).

